## **4.1.2. Respiratory Infection susceptibility in athletes-illness prone profile (II)**

This is a prospective, three month follow-up, cohort study to evaluate the risk factors for respiratory infection. A group of swimmers from a Porto sports team (Futebol Clube do Porto), from a high competition level and active during the follow-up period, which is coincident with a pre-competition season and higher incidence of respiratory infections (from January to March). During this time participants will be followed for respiratory infections episodes through a daily respiratory infections questionnaire, which is filled in when they began respiratory infections symptoms and then everyday during the scheduled-time illness. Acute respiratory infection number, duration severity of each episode will be characterized. All potential risk factors for respiratory infections will be evaluated at baseline and at the end of the study, except for urine analysis which will be collected every week and during the respiratory infection episode to establish an eventual association between changes of urinary metabolome in and outside the infection period.

### **Participants**

All elite swimmers of Porto Sports Club from the main swimming team who are annually screened for asthma and atopy at Allergy Asthma and Sports Unit will be invited to participate in the project. The inclusion criteria will be: competitive level swimmer; aged above 16 year-old; either sex and of any race. A potential subject who meets any of the following criteria will be excluded from participation in this study: neurological or psychiatric illness which enable them to fill in the formulary/ and questionnaires and anything that, in the opinion of the investigator, would place the subject at increased risk or preclude the subject's full compliance with or completion of the study. All these participants were previously included in the study, "*Mechanisms of airway damage in elite swimmers*" that was previously submitted and accepted in the Ethical Commission for Health of Centro Hospitalar de São João. For being included in this project written information about this follow-up will be provided and informed consent will be signed.

### **Procedures**

Participants recruited in the previous project "*Mechanisms of airway damage in elite swimmers*" and all those that fill in the inclusion criteria, accept to participate and sign the informed consent will be evaluated at baseline.

In baseline the following characteristics and potential risk factors for respiratory infections will be screened:

- demographic data; full clinical history (namely asthma, respiratory or cardiovascular disease); chronic medication (any medication taken oral or inhaled); time of exercise practice and intensity of the trainings; immunization status and influenza vaccine; use of pro-biotics or vitamin supplements

- anthropometric and bio-impedance measures;
- nutritional state assessment and nutritional questionnaires (see description in measurements)
- sleep quality assessment questionnaires (**Attachment 3**) and anxiety symptoms questionnaire (Zung Self Rate Anxiety Scale- **Attachment 4**)
- lung function (espirometry), airway inflammation evaluated by induced sputum evaluation, airway hyper-responsiveness (methacholine provocation testing), bronchial challenge with inhaled capsaicin, exhaled nitric oxide measurement (*performed in the “Mechanisms of airway damage in elite swimmers” project-accepted by the ethical commission Centro Hospitalar de São João Attachment 5*)
- cholinergic-parasympathetic system measure by pupillometry response (*performed in the “Mechanisms of airway damage in elite swimmers” project-accepted by the ethical commission of Centro Hospitalar de São João Attachment 5*)
- blood withdraw for inflammatory cytokines measurement
- exhaled breath condensate, exhaled breath
- urine collection for metabolome measurements

During the follow-up it will be monitored through a respiratory infections questionnaire the episodes of respiratory infections, duration, severity and quality of life impact. A diary of all missed trainings will be kept during the follow-up period. Urine samples will be obtained every week and during the infections period.

Participants will also be submitted to a nutritional 24h dietary recall interview twice a month. The first one will occur at baseline and will be performed face-to-face with the investigator, so that the participant understand the purpose of the interview and also could be trained in the procedure. The following recalls will be assessed by telephone.

At the end of the follow-up period participants will perform:

- anthropometric and bio-impedance measures;
- nutritional state assessment and nutritional questionnaires;
- sleep quality assessment questionnaires and anxiety symptoms questionnaire (Zung Self Rate Anxiety Scale-- **Attachment 4**);

All variables will be assembled at the end of the study and individuals with respiratory infections during this period will be compared with those without the outcome. Associations will be performed *a posteriori* between urine metabolome analysis and the days with respiratory infections and before/after an infection episode.

### **4.1.3. Effect of Physical training on respiratory tract infection in the elderly (III)**

*This study was previously presented and accepted by the ethical commission of Centro Hospitalar de São João (Attachment 6)*

The study was a non-randomized, un-blinded, controlled trial targeting patients over 60 years recruited by the Exercise Health for the Elderly program, coordinated in Sports Faculty of Porto University, from senior universities and nursing homes from Northern Portugal area. The selected participants performed a 36 week, 3 times per week, exercise-training program in the Sports University of Porto, with aerobic and anaerobic components using an individualized protocol by trained sports personal. During this period of time, respiratory tract infections were monitored through a symptoms diary and respiratory infections were defined as severe, moderate or mild accordingly to the symptoms assembly. Previously to the intervention a global physical condition was assessed (weight, height, heart rate, functional fitness and blood pressure were measured), co-morbidities were registered (hypertension, dyslipidemia, diabetes, ischemic heart disease, previous stroke, previous cancer diseases, osteo-articular and osteoporosis), as well as smoking habits, influenza immunization status and if they previously practiced exercise.

#### **Participants**

Recruitment occurred from September until November 2010 through Exercise Health for the Elderly program, organized by The Research Centre in Physical Activity, Health and Leisure, at Faculty of Sport Sciences and Physical Education at the University of Porto, which receives patients from the Porto metropolitan area, Senior Universities from Porto and also nursing homes and daily care centers for the elderly in Northern region of Portugal. Participants were contacted by phone or personal contact at the universities or nursing homes. Intervention group participants belonged mainly from Porto metropolitan area, as they had the ability to travel to the training sessions that occurred at Faculty of Sport Sciences and Physical Education at the University of Porto. Control group were recruited from nursing rooms and daily care centers from Paredes de Coura, and all of those from Porto metropolitan area which were not able to participate in the intervention group by schedule incompatibilities. Participants were eligible if they had: over sixty years old, a medical report describing that they were physically able to practice aerobic and anaerobic exercise of moderate intensity and did not participated in previous physical exercise programs. Exclusion criteria included all patients with uncontrolled disease, namely hypertension, patients with cardiac or orthopedic prosthesis, patients with a psychological, familial or sociological problem that might compromise their compliance to the exercise program. Participants were provided with written information about the exercise training program and symptoms diary data collection. A total of 80 patients were recruited for

the study, 12 did not meet the eligibility criteria and 30 refused to participate, so 38 patients were selected. Participants were then assigned to the training group and control group accordingly to the availability and proximity to the exercise training group.

## Procedures

### Exercise program

Exercise program was performed during 36 weeks and consisted in 3 times per week in non-consecutive days (Mondays, Wednesdays and Fridays). Each session was performed in group with all elements and included a 30 minutes aerobic training and 45 min of anaerobic training. Aerobic training consisted in 30 min walking at moderate intensity reaching 60-80% of the maximum heart rate (*monitored by polar team system, Finland*). Resistance or anaerobic training was performed during 45 min aiming 9 different muscular groups (leg press, chest press, leg extension, seated row, seated leg curl, abdominal flexion, low-back extension, biceps curl and triceps extension), each exercise was performed twice with 10 to 12 repetition at 60-80 % of repetition maximum (repetition maximum for each patient was previously calculated on base of *Epley formula*). Training was standardized, but adapted to each participant difficulties or handicaps, namely accordingly to previous osteoarticular conditions.

Intervention and control group were submitted first to a demographic, previous history of cardiovascular, osteoarticular, cancer or respiratory diseases, smoking habits, influenza immunization and history of previously practiced exercise. Baseline weight and height was also collected.

### Respiratory Infections Symptoms Diary

For respiratory infections measure it was used a symptom diary, based in previously published symptoms diaries and common cold assessment questionnaires based in the Jackson index, Common Cold Questionnaire and Wisconsin diary symptoms short form-survey[45, 46]. The diary was built to answer to the specific demands of the population, namely age, real life conditions of the study as no patients with chronic previously reported respiratory diseases were excluded. Through this symptom diary it would be possible to quantify respiratory infections, their severity and duration. The questionnaire was subdivided in five main symptoms categories, similarly as occurred in the common cold questionnaire, but also including ear and eye symptoms. Furthermore allergy symptoms were included, namely nose and eye itching to exclude allergic symptoms in the evaluation of the symptoms diary. Patients were also requested to fill in if they had any symptoms and those symptoms reported in every and most of the days during the intervention study were excluded, as they were probably reported by patients with chronic respiratory diseases. The five domains were: general symptoms (shivering, muscle pain, tiredness, chest pain, dispnea), nasal symptoms (runny nose, obstructed nose, sneezing, nose itch), eye symptoms (itching eyes), throat symptoms (sore throat, itching throat, cough and hoarseness) and ear symptoms (ear pain) and body temperature. Temperature was

registered if the absolute value met above 37.5°C. Each symptom would be classified accordingly to the severity in a likert scale from 0 to 7.

A pilot study was performed with an elderly population already in an exercise program and due to difficulties in filling the Likert scale it was adapted to classification of the symptoms when present in mild, moderate or severe.

All participants was given a symptom diary, and explained individually how it should be filled, also a written explanation was provided in the questionnaire itself. Symptoms diary should be filled daily if any of the symptoms was experienced. A contact to the investigator was provided if any questions or doubts were present. All participants were contacted telephonically each month to maintain compliance and questioned if they were still in the trial, if they had been sick or had any problem filling in the questionnaire. The questionnaire could also be filled by a third person if the participant was not able to read. In the nursing home the responsible for the elderly was also trained to know how the questionnaire should be filled.

#### **4.1.4. Effect of an high fat meal on neuro-immune-endocrine response to an acute exercise challenge (IV)**

This is a randomized cross-over trial, with a wash out period of 7 days, single-blinded, placebo controlled. Study design is specified in figure 1. Participants will be recruited from advertisement and four different groups will be compared: obese-asthmatic; asthmatic non-obese; obese without asthma and non-asthmatic and non-obese. Stratification will be done accordingly to having asthma and  $BMI \geq 30 \text{ kg/m}^2$ . All patients will be allocated to a meal challenge in which a high fat meal will be followed by a low fat meal or vice-versa, meal challenge order will be randomized and participants blinded to the intervention. Three hours after it will be followed by an exercise challenge, which is aimed to induce acute immune changes. The main outcome will be exercise-immune function (immune function markers) changes after a diet challenge. As secondary outcomes stress/inflammatory markers, endocrine mediators, as well as blood fatty acids will be measured. Lung function,  $VO_2$  and airway inflammation will be assessed by exhaled breath condensate inflammatory markers and eNO. Any adverse events of the challenge will be registered, namely respiratory infections, gastro-intestinal symptoms and muscular ache.

[figure not shown]

**Figure1.** Randomized cross-over study trial, single-blinded to meal intervention. Measures (1.1; 1.2;2.1;2.2) immediately before and after exercise challenge include: Immune-endocrine-metabolomic response (blood, urine and saliva samples); Pupilometry; Lung-function and VO2 consumption; skin prick histamine reactivity

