### **Methods:**

Study design: An observational study with validation methodology will be applied to evaluate respiratory infections; in prospective cohort study of 12 weeks a group of athletes under high competition levels, respiratory infections and potential risk factors accordingly to literature will be evaluated; an prospective case-control with a moderate- exercise program intervention will compare the impact in respiratory infections in elderly under exercise training or not; a randomized, placebo controlled cross-over trial will evaluate the impact of a high fat/high energy meal challenge in an acute exercise challenge; randomized clinical trial will be used to ascertain the impact of physical activity reduction in the immune function

Selection of participants: For questionnaire validation will be selected participants with respiratory infections; athletes will be selected from a high elite pre-competition level team; elderly will be selected from general population, namely from senior universities and nursing homes; asthma and obese participants will be selected from an university population sample

Sample Size: 281 patients will be chosen as target for evaluation in respiratory tract infections validation; 40 patients will be evaluated in total in swimmers illness-prone study trial; 40 participants will be selected to evaluate exercise program in the elderly; 30 participants, with a

equal number of obese, asthma, obese and asthma and a control will be allocated to the meal interventions (60 participants in total) and a target of 60 participants will be randomized to the physical inactivity intervention.

Measurements: Upper respiratory tract infections number, severity and quality of life impact, immune system markers, complete blood cell count, pro-inflammatory and anti-inflammatory mediators, namely cytokines, and metabolomic.

Main Outcomes: Respiratory Infection Risk in Susceptible Population, Immune markers parameter related with acute exercise and physical inactivity interventions (balance between pro-inflammatory and anti-inflammatory cytokines).

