### Randomization and blinding

Patients will be informed of the procedure but they will be blinded to which is the intervention (high fat or low fat meal). Stratified blocked randomization will be performed accordingly to being asthmatic or obese. This methodology was chosen despite acute changes are the aim, to exclude and evaluate the intervention order in the studied outcomes. Equal number of participants will be allocated to each group.

Allocation concealment will be prevailed as investigator will only know the intervention order for that participant at the moment the meal is provided. Exercise challenge and outcome assessment, namely urine, blood sample collection, exhaled breath condensate and lung function will only be performed by another investigator blinded to the meal order.

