#### **4.2.8. Meal challenge (IV)**

All individuals will be asked to consume two different meals, an high fat/high energy meal and another low fat/low energy. The high-fat/high energy meal will by characterize by: total energy (TE) approximately of 1600kcal, consisted of 40g protein (9,6% TE), 218g carbohydrate (55% TE), and 60g total fat (34% TE) and 18g saturated fat (10% TE). The other meal will be according to the Portuguese guide - Roda dos Alimentos[58], characterized with low-fat/low energy meal: TE approximately with 660kcal (1/3 of 2200kcal), consisted of 50 to 70% TE of carbohydrate, 30% TE of total fat and less than 10% of saturated fat.

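### Study IV is labelled placebo controlled with blinded participants, yet each participant eats both a meal of about 1600 kcal and one of about 660 kcal with no masking described; only the assessor blinding is credible

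*Protocol*

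**What the plan says.** The opening of Protocol section 4.1.4 sets the design: "This is a randomized cross-over trial, with a wash out period of 7 days, single-blinded, placebo controlled". It continues that "meal challenge order will be randomized and participants blinded to the intervention", and the legend to Figure 1 repeats the single-blind label with respect to the meal. The Methods part of the Summary says that "a randomized, placebo controlled cross-over trial will evaluate the impact of a high fat/high energy meal challenge", and the Portuguese Resumo says the same.

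The Randomization and blinding part of 4.1.4 makes two separate statements. The first covers participants, who know the procedure but not which meal is the intervention. The second covers staff: the exercise challenge, the sampling and "lung function will only be performed by another investigator blinded to the meal order".

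Section 4.2.8 describes the meals: "All individuals will be asked to consume two different meals, an high fat/high energy meal and another low fat/low energy". The first has "total energy (TE) approximately of 1600kcal, consisted of 40g protein (9,6% TE), 218g carbohydrate (55% TE), and 60g total fat (34% TE"). The second follows the Portuguese food guide, at about 660 kcal, which the text explains as one third of 2200 kcal, with 30% of energy from fat. The Intervention part of 4.1.4 has leftovers on the plate recorded. Nowhere is a placebo or sham meal, matching for volume or energy, or disguise of the food described.

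**The concern.** Two stated design properties do not fit the described conduct. A placebo-controlled trial needs an inert comparator made to look like the test treatment; here the comparator is an ordinary meal. Participant blinding requires that participants cannot tell the meals apart, yet in this cross-over each person eats both and can compare them.

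The consequence lies mainly in the measurements that depend on effort or self-report. The Intervention part of 4.1.4 asks for maximum effort on the treadmill. Section 4.2.9 sets the workload by the highest speed the participant can sustain. Spirometry needs forced manoeuvres, and symptoms are reported by the participant. A person who knows which meal was eaten may run, blow or report differently. Since the exercise is there to provoke the immune response, a systematic difference in effort between meals could also reach the primary immune markers, by that indirect route. A report that repeats the present labels would claim a protection that the study lacks on the participant's side.

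**Working it through.** **Inputs (section 4.2.8).** High-energy meal: about 1600 kcal, with 40 g protein, 218 g carbohydrate, 60 g fat and 18 g saturated fat. Low-energy meal: about 660 kcal, given as one third of 2200 kcal, with 50 to 70% of energy from carbohydrate and 30% from fat. Assumption not in the protocol: 4, 4 and 9 kcal per gram of protein, carbohydrate and fat.

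**1. Reproduce the high-energy meal.** 40×4 + 218×4 + 60×9 = 160 + 872 + 540 = 1572 kcal, against about 1600 stated (28/1600 = 1.75% lower). Shares of 1600 kcal: protein 160/1600 = 10.0% (stated 9.6%), carbohydrate 872/1600 = 54.5% (55%), fat 540/1600 = 33.8% (34%), saturated fat 18×9/1600 = 10.1% (10%). The figures agree.

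**2. Reproduce the low-energy meal.** 2200/3 = 733 kcal, whereas 660/2200 = 30%. The stated energy and its stated derivation differ, so both values are carried forward.

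**3. Energy contrast.**

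| High meal (kcal) | Low meal (kcal) | Difference (kcal) | Ratio |
|---|---|---|---|
| 1600 | 660 | 940 | 2.42 |
| 1572 | 660 | 912 | 2.38 |
| 1600 | 733 | 867 | 2.18 |
| 1572 | 733 | 839 | 2.14 |

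**4. Fat contrast.** Low meal: 0.30×660/9 = 22.0 g, or 0.30×733.3/9 = 24.4 g. Ratios: 60/22.0 = 2.7 and 60/24.4 = 2.5.

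**5. Carbohydrate contrast.** Low meal at 660 kcal: 0.50×660/4 = 82.5 g to 0.70×660/4 = 115.5 g. At 733 kcal: 0.50×733.3/4 = 91.7 g to 0.70×733.3/4 = 128.3 g. Ratios run from 218/128.3 = 1.7 to 218/82.5 = 2.6. The fat shares are close (34% against 30%), so the meals differ mainly in how much fat and carbohydrate is served, not in the mix.

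**6. Set against the blinding statements.** In period 2 the participant has eaten one meal about a week before and now eats the other, which differs more than two-fold in energy. Nothing described would hide this. In period 1 there is no second meal for comparison, so recognition is less certain. The protocol gives no basis for a rate of correct guessing in either period, and the conclusion needs none.

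**7. Set against the assessor blinding.** The size of the meal does not tell the exercise and assessment investigator which meal was served. That blinding can fail through the participant's own remarks, and 4.1.4 contains no instruction against disclosure.

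**The case against.** The case on the other side has several parts.

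- **Staff blinding is planned.** A reader might infer that Study IV has no blinding at all. The protocol does not support this: a separate investigator, blind to meal order, runs the exercise challenge and collects the outcomes. This stands, and the point is limited to participants.
- **The participant statement may mean less.** "Patients will be informed of the procedure but they will be blinded to which is the intervention (high fat or low fat meal") can be read as hiding only which meal is the test condition. A reader might also infer that participants are told outright that the meals are high and low in fat. The document does not show this. Section 6 says the aims are explained, and section 3 gives the aim as high fat against a healthy meal, but the participant information itself is not available here. The softer reading is possible. It is weaker than the blinding to the meal that the opening of 4.1.4 and Figure 1 claim.
- **Energy is not appearance.** Menu and volume are not given, so a visible difference is an inference. It is a fair one, because the meals differ mainly in amount (working, steps 3 to 5) and no matching is mentioned.
- **Effort is partly controlled.** Speed is adjusted towards about 95% of a reference heart rate, heart rate is monitored throughout, and VO2 and heart rate are measured at the end. This stands and narrows the route to bias. It does not close it, because speed and duration are still set individually. The reference heart rate is also written in two ways, 220 minus resting heart rate in 4.1.4 and 220 minus age in 4.2.9; these need to be reconciled.
- **The main outcome is a laboratory measure.** This stands. Symptoms, moreover, are not listed as a secondary outcome in 4.1.4: they are recorded during exercise and as adverse events.

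**Conclusion.** The point holds in limited form. The placebo label is wrong: no placebo exists. Participant blinding to the meal is not credible as described, above all in period 2, given a 2.1- to 2.4-fold difference in energy and about 60 g against 22 to 24 g of fat. The blinding of the exercise and outcome investigator remains credible if participants do not disclose the meal.

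VO2, spirometry and reported symptoms are therefore open on the participant's side, but not, as planned, on the assessor's side. A reader might go further and infer that the primary immune markers are directly biased. The documents do not support that: they are laboratory measures, exposed only through the exercise actually done, which the heart-rate target partly standardises.

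The conclusion assumes that the meals are served as section 4.2.8 describes, without masking left unmentioned. It does not depend on which value of the low meal is used, nor on any assumed rate of correct guessing. No change to randomisation or to the primary endpoint follows. What changes is what the study may claim about its blinding.

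**What to change.** - Delete the placebo-controlled label from the Summary, the Resumo and section 4.1.4.
- In 4.1.4, including the Figure 1 legend and Randomization and blinding, describe Study IV as outcome-assessor-blinded, with participants not reliably blinded to the meal.
- Instruct participants not to reveal the meal to the exercise and assessment team.
- Report achieved treadmill speed, duration and heart rate by meal, so that a difference in effort can be seen.
- State that VO2, spirometry and reported symptoms are interpreted as open on the participant's side.
- Reconcile the stated 660 kcal with its stated derivation as one third of 2200 kcal.

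The cost is a slightly less favourable description of the design, one added instruction, and the logging of speed and duration where this is not already done. Heart rate is already monitored. The meals and the exercise procedure stay as they are.
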